#### Sample size

A sample size of 84 subjects was estimated, considering a crossover clinical trial design as proposed by Hills and Armitage [70], accepting a type I error of 0.05, a power of 90%, and assuming a difference of 20 % in the HOMA index after 6 months of treatment with Candesartan (3 to 2.4) and a maximum standard deviation of 1.5. The final size of the sample, adjusted for a drop-out of 8%, is 100 subjects (50 in each group). The sample size ensures a power of 90% to detect differences in fasting glycemia of at least 8 mg/dL (0.44 mMol/L) with a standard deviation (SD) of 20 mg/dL (1.1 mMol/L), or a difference of 14 mg/dL (0.77 mMol/L) in the 2 hours post load glycemia with a SD of 40 mg/dl (2.2 mMol/L).

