### Statistical analysis

The study is set forth as an efficacy study of Candesartan in the improvement of the insulin sensibility and the OGTT results. The averages and proportions with their corresponding 95% confidence intervals will be obtained in a descriptive analysis for all clinically relevant variables measured during the baseline evaluation. In order to evaluate the presence of differences between the groups, the Student's paried *t- *test, the Wilcoxon's signed-rank test or the McNemar's test will be used according to the variable's characteristics. Linear multiple regression will be used with the purpose of comparing the results of the treatments. The analysis will be performed by the intention-to-treat approach. A p value under 0.05 will be considered as statistically significant.

The primary endpoint for the analysis will be the change in the value of HOMA index, fasting glucose and post-charge glucose plasma levels. The secondary endpoint for the analysis will include the changes in serum insulin, leptin, adiponectin, resistin, CRP, IL-6, tPA/PAI-1 ratio, Oxidized/Reduced glutathione ratio, malonaldehyde and 8-isoprostanes.

Treatment safety will be evaluated by the clinical history review and the statistics of the reported adverse events.

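### Three unranked primary variables share one p<0.05 threshold with no success rule: about 8–14% false-positive risk if any one suffices, about 82–89% joint power if all three must succeed

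*Protocol article*

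**What the plan says.** The Statistical analysis section defines the primary endpoint in one sentence: "The primary endpoint for the analysis will be the change in the value of HOMA index, fasting glucose and post-charge glucose plasma levels". It gives one significance criterion for the whole analysis: "A p value under 0.05 will be considered as statistically significant". It sets no order among the three variables, no division of alpha and no statement of what counts as a positive trial.

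The Sample size section derives the number of patients from HOMA alone: "accepting a type I error of 0.05, a power of 90%, and assuming a difference of 20 % in the HOMA index", with the effect and spread given as "after 6 months of treatment with Candesartan (3 to 2.4) and a maximum standard deviation of 1.5". It then claims, for the same number of patients, a "power of 90% to detect differences in fasting glycemia of at least 8 mg/dL" with an SD of 20 mg/dL. It makes the same claim for a 14 mg/dL difference in 2-hour glucose with an SD of 40 mg/dL. All three variables were therefore considered for power, each on its own.

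Other sections do not settle which variable leads. The Abstract hypothesis names HOMA and the OGTT response. The Hypothesis section in the body names fasting plasma glucose and not HOMA. The Statistical analysis section opens with insulin sensitivity and the OGTT.

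**The concern.** A primary analysis of three variables needs a success rule, because the rule determines both the error rate and the power. Without one, the result can be read after the fact in whichever way suits the data: a single p-value below 0.05 can be presented as a positive trial, or a miss on one variable as a negative one.

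If one of three is enough, the 0.05 that the plan accepts is the error rate of each test and not of the primary conclusion. If all three are needed, the 90% that the plan claims is the power for each variable and not for the trial. The ambiguity cannot be credibly removed once results are known.

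**Working it through.** **Inputs from the protocol article.** Three primary variables and a threshold of 0.05 (Statistical analysis). From Sample size: 84 evaluable patients in a crossover; HOMA difference 3 − 2.4 = 0.6 with SD 1.5; fasting glucose 8 mg/dL with SD 20; 2-hour glucose 14 mg/dL with SD 40; target power 90%.

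**Assumptions.** Tests are two-sided (sidedness is not stated). Each SD is the SD of the within-patient difference (the article does not say). Correlations between the three test statistics run from 0 to 0.9. They are not given, but some positive correlation is expected because HOMA is calculated from fasting glucose.

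**1. The plan's own sample size.** For a crossover, n = [SD × (1.960 + 1.282) / difference]².
- HOMA: 0.6/1.5 = 0.40, so n = (3.242/0.40)² ≈ 66.
- Fasting glucose: 8/20 = 0.40, so n ≈ 66.
- 2-hour glucose: 14/40 = 0.35, so n = (3.242/0.35)² ≈ 86.

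The HOMA inputs do not return 84 under this reading. That is a separate matter and does not alter the point here. At n = 84 the power of each test is Φ(effect × √84 − 1.960):
- HOMA and fasting glucose: Φ(3.666 − 1.960) = 95.6%.
- 2-hour glucose: Φ(3.208 − 1.960) = 89.4%.

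**2. If any one of three suffices.** For independent tests, the chance of at least one false positive is 1 − 0.95³ = 14.3%. For correlated tests, simulation of three correlated normal statistics (4 million draws) gives:

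| Common correlation | At least one p<0.05 under no effect |
|---|---|
| 0 | 14.3% |
| 0.3 | 13.6% |
| 0.5 | 12.6% |
| 0.6 | 11.8% |
| 0.7 | 10.9% |
| 0.8 | 9.9% |
| 0.9 | 8.4% |

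Unequal correlations of 0.5, 0.3 and 0.4 give 13.1%; 0.7, 0.5 and 0.6 give 11.7%.

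**3. If all three must be significant.** Type I error is at most 5%. Joint power at 84 completers is 0.956 × 0.956 × 0.894 = 81.7% if the tests are independent, and 88.5% by simulation at a common correlation of 0.9. It cannot exceed the 89.4% of the weakest test. Taking the plan's claim of 90% for each variable at face value gives the same conclusion: 0.90³ = 72.9% if independent, and never more than 90%.

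**4. Under Holm with three primaries.** The first-step alpha is 0.05/3 = 0.0167. With 84 completers (noncentral t, 82 degrees of freedom), power is about 89% for HOMA and for fasting glucose, and about 78% for 2-hour glucose.

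**The case against.** The strongest counter-argument is that no inflation is proven. The article speaks of one primary endpoint, joins the three variables with 'and', and reports power for each, which fits an intention to require all three. Under that rule type I error does not exceed 5%. A reader might infer from the wording that the trial's false-positive rate simply is 12–14%. The document does not support this. The figure holds only if any one result counts as success, and only for correlations up to about 0.6; with the overlap between HOMA and fasting glucose it could be nearer 8–10%.

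A reader might also infer that the plan promises 5% error across the three tests and breaks that promise. It does not: Sample size accepts a type I error of 0.05 without saying that it covers all three. Nor do the secondary markers add to the problem, since they are labelled secondary.

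It can also be said that a testing hierarchy often sits in an SAP, which is not shown here. That is fair as to the procedure. But the choice of three unranked primaries with one flat threshold is made in this document, and its sections differ on which variable leads.

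Finally, 84 is close to the 85 patients that HOMA would need at alpha 0.0167: [(2.394 + 1.282)/0.40]² = 84.4. This might suggest a planned Bonferroni correction. The stated alpha of 0.05 rules out that reading.

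**Conclusion.** The concern holds as an undefined success rule, not as a demonstrated error rate. Read as any of three, the false-positive risk for the primary conclusion is about 8–14%, above 5% at every correlation examined. Read as all three, the error is controlled but joint power is about 82–89%. The first range rests on assumed correlations and two-sided tests. The second also rests on treating the stated SDs as SDs of within-patient differences. Under those assumptions, neither reading yields both 5% error and 90% power. Because the gap concerns the primary conclusion, it should be closed before unblinding.

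**What to change.** Name the change in HOMA as the single primary endpoint at two-sided 0.05. Then test fasting glucose and 2-hour glucose in a prespecified order, each at 0.05 and only if the preceding test is significant. Keep all other markers secondary. HOMA is the natural choice because the 84 is attributed to it, and the Hypothesis section should be aligned accordingly. Fasting before 2-hour glucose follows the article's list order and its larger standardised effect (0.40 against 0.35). The sponsor may prefer the reverse on clinical grounds, provided that the order is fixed in advance.

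This holds the error across the three tests at 5%, adds no patients and leaves HOMA about 95% power at 84 completers under the same SD assumption. The cost is that the glucose endpoints lose stand-alone confirmatory status. The last variable in the sequence is reached and significant only with the 82–89% joint power shown above.

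If the sponsor wants three primaries, state that any one suffices, use Holm's procedure, and restate the power in Sample size with the first-step figures above. The 2-hour glucose would then fall short of the claimed 90%: at alpha 0.0167 it needs [(2.394 + 1.282)/0.35]² ≈ 111 evaluable patients. If all three are required instead, say so and report the joint power.

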### Safety committee and events assignation committee

A safety and events assignation committee will be created, according to the Harmonized Tripartite Guidelines of the International Conference of Harmonization for Good Clinical Practice.

### Ethical aspects

The clinical trial will be conducted according to the Helsinki's Declaration, the Good Clinical Practice Guidelines and the Colombian legislation (Resolution 8430/93 of the Ministery of Health). The patient will provide written informed consent in a form designed for such purpose. The information generated by the study will be confidential and strictly limited to the purposes stipulated in the protocol. The patient may refuse to continue participating in the study at any moment after providing his/her consent. The study has been approved by FVC ethics committee. All assessments will be performed by trained staff. The blood samples will be collected in aseptic conditions by an expert bacteriologist.

### Study timeline

The study will last 36 months. The initiation will be defined by the financial approval from the sponsor(Figure 3.).

**Figure 3 F3:**
[figure not shown]
**title**. Study Timeline.

## Abbrebiations

**(ACE) **Angiotensin Converting Enzyme

**(ACEIs) **Angiotensin Converting Enzyme Inhibitors

**(ADA) **American Association of Diabetes

**(AII)**Angiotensin II

**(AT_1_) **Angiotensin II Type 1 Receptor

**(AT_2_) **Angiotensin II Type 2 Receptor

**(BMI) **Body Mass Index

**(CRF) **Case Report Form

**(CRP) **C-reactive Protein

**(CVD) **Cardiovascular Diseases

**(DBP) **Diastolic Blood Pressure

**(DM2) **Type-2 Diabetes Mellitus

**(eNOS) **Endothelial Nitric Oxide Synthase

**(FAS) **Fatty Acid Synthase

**(FCV)**Fundacion Cardiovascular de Colombia

**(FFA) **Free Fatty Acids

**(FMD) **Flow-Mediated Dilation

**(GDPH) **Glycerol-2 Dehydrogenate Phosphate

**(HOMA) **The Homeostasis Model Assessment

**(IFG) **Impaired Fasting Glucose

**(IGT) **Impaired Glucose Tolerance

**(IL-6) **Interleukine 6

**(IRS-1 and IRS-2) **Insulin Receptor Substrate Type 1 and 2

**(MBP) **Mean Blood Pressure

**(MMP-2) **Matrix Metalloproteinase-2

**(NADPH) **Nicotinamide Adenine Dinucleotide Phosphate Hydrogen

**(NO) **Nitric Oxide

**(OGTT) **Oral Glucose Tolerance Test

**(PAI-1) **Plasminogen Activator Inhibitor-1

**(PKC) **Proteinkinase C

**(PPARs) **Peroxisome Proliferator-Activated Receptors

**(RAS) **Renin-Angiotensin-Aldosterone System

**(ROS) **Reactive Oxygen Species

**(SBP) **Systolic Blood Pressure

**(SD) **Standard Deviation

**(TLC) **Therapeutic Life-Style Change Program

**(TNF-α) **Tumor Necrosis factor alpha

**(tPA) **Tisular Plasminogen Activator

**(UPC-2) **Uncoupling Protein 2

**(W/H-R) **Waist-Hip Relation
